#### Economic evaluation

Economic evaluation methods will, as far as possible, adhere to the recommendations of the NICE Reference Case [37]. The economic evaluation will consist of a within-trial analysis and economic modelling. Within trial analysis will compare direct costs and six month outcomes of patients randomised to intervention versus control. The perspective adopted will be that of the NHS and Public Social Services. A costing study will record intervention costs (to include staff time, capital, overheads and consumables), other NHS resource use (e.g. general practitioner visits) and patient expenditure. Unit costs for health care resources will be derived from local and national sources and performed in line with best practice [38]. Costs will be standardised to current prices where possible. Because of the short follow up period, we will not discount costs or benefits.

Comparison will be made between baseline and 6 months to estimate incremental cost-effectiveness ratios (ICERs) comparing the intervention with the control group in terms of the primary outcome measure (mean daily minutes walked in the past week) and costs [30]. Quality of life (EQ-5D) over the study period will be used to generate quality-adjusted life-years (QALYs) [39]. Outputs will be presented as ICERs, cost-effectiveness acceptability curves and expected net benefit. Sensitivity analyses will consider key cost drivers and factors that might affect the outcomes measured in order to explore uncertainty in the conclusions drawn.

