### Outcome measures

The main outcome measure will be mean daily number of minutes walked in the past week, assessed at all time points using the New Lifestyles NL-1000 Activity Monitor Pedometer (New-Lifestyles Inc, Lees Summit, Missouri, USA). This pedometer provides readings on number of minutes walked and step counts, over each of the previous seven days. The intensity threshold of each pedometer will be set to record movement on a setting of four or above (the range is 1 to 9), to assess physical activity of at least moderate intensity.

Psychological process will be assessed using one of two Theory of Planned Behaviour (TPB) [15] questionnaires, both of which measure several constructs. A longer 26-item version measures intentions, self efficacy/ PBC, attitudes, subjective norms, control beliefs and associated perceived power to inhibit/ facilitate behaviour in relation to walking for at least 30 minutes on average a day over the next 7 days [29]. A brief 6-item version of the questionnaire assesses only intentions, self efficacy/ PBC, attitudes, and subjective norms. Both versions of the TPB questionnaire are abbreviated versions of measures previously developed [10] and validated [13,14] in studies of walking with an adult volunteer general public sample.

Data on NHS resource use and personal costs to patients will be collected using standard measures for economic analysis [30]. Impact on Quality of Life will also be assessed using the EQ-5D questionnaire [31,32]. Comparing this with costs (directly and indirectly related to patient management) will enable incremental cost-effectiveness of the intervention to be estimated.

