#### Patient consent, receipt of intervention, and follow-up measurements

For both experimental conditions, each patient attends a face-to-face session at their own practice with the PN/HCA who is delivering the session. During this session, they are screened for whether they already do more than 30 minutes of moderate or vigorous physical activity per day on at least 5 days a week. If they are not already achieving this recommended level of physical activity, they are asked to provide informed consent, and complete the baseline (t1) questionnaire, which includes the full TPB measure, the EQ5D, and measures of ethnicity, employment status and education level. Information on patient date of birth, gender, and the clinical condition for which they were flagged (e.g. diabetes, hypertension, etc) will be recorded on a standardised form by PN/HCAs. The form will be sent to the research team, along with their contact details. Weight and height information for each patient will be recorded by the PN/HCA at baseline, which will allow calculation of body mass index. After this point, the procedure differs for patients in practices allocated to the self-regulation intervention condition, and patients in practices allocated to the information provision condition (see Figure 1).

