**Figure 1 F1:**
[figure not shown]
**Flowchart showing planned study recruitment numbers, and timing of intervention sessions and measurements**.

For patients in practices allocated to the information provision control condition, the session will continue with delivery of the "information provision" intervention as described above: the PN/HCA will provide their patients with an information pack of materials promoting walking, and answer any questions the patient may have about walking more. At the end of this session, patients complete the post-intervention (t2) questionnaire, consisting of the brief TPB measure only, and are given a pedometer, with detailed instructions in its use. They are asked to wear it for a week, and return to the research team in a reply-paid envelope. This forms the first post-intervention assessment of walking.

For patients in practices allocated to the self-regulation intervention condition, the PN/HCA provides their patients with an information pack of materials promoting walking, and answers any questions the patient may have about walking more. Following this, two further face-to-face appointments will be booked, for delivery of the self-regulation intervention (as described above), at one week and two weeks after this initial session, plus the final intervention session four weeks after the initial session. At the end of this session, patients are given a pedometer, with detailed instructions for its use. They are asked to wear it for a week, and return it at their first intervention session where the PN/HCA will extract the data from the pedometer. This initial assessment of walking constitutes a pre-intervention measurement for those patients in the intervention arm.

Patients in practices allocated to the intervention condition then receive the self-regulation intervention, as detailed above. Sessions one and two will be tape-recorded, with the explicit agreement and signed consent of the patients involved. At the end of the second face-to-face session, patients complete the post-intervention (t2) questionnaire, and are given a pedometer, to wear for a week, and then return to the research team in a reply-paid envelope. This forms the first post-intervention assessment of walking.

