Patients in practices allocated to the intervention condition receive a final follow-up intervention session, which may be by telephone or face-to-face, two weeks after their second face-to-face session. Despite this, the measurement procedures for patients in practices in both conditions are identical from t2 onwards.

At six weeks post intervention (i.e. six weeks after t2 for both groups), all patients are sent a questionnaire by post (t3) containing the brief TPB measure, and a pedometer, and asked to return these by post. At six months post intervention (t4), all patients are sent a questionnaire containing a full TPB measure, the EQ5D, and a final pedometer, which again they are asked to return by post.

To encourage retention, all participants who complete and return questionnaires or pedometers from t2 onwards will be sent postal feedback on their walking behaviour and psychological measurements in the form of a postal profile. Those who do not send back the pedometer at any measurement point will receive a reminder letter and follow-up telephone calls from the research team encouraging them to return these, as loss of numerous pedometers will be expensive, and threaten the validity of the study.

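### The walking cost-effectiveness ratio is set on a baseline-to-six-month comparison that cannot be computed for controls, and the time from baseline to final follow-up differs by two weeks between arms

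*Protocol article*

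**What the plan says.** In the protocol article, Economic evaluation, the rule for the walking ratio is: "Comparison will be made between baseline and 6 months to estimate incremental cost-effectiveness ratios (ICERs) comparing the intervention with the control group", and the effect is expressed "in terms of the primary outcome measure (mean daily minutes walked in the past week) and costs". Earlier in the same section the within-trial analysis is described without reference to baseline: "Within trial analysis will compare direct costs and six month outcomes of patients randomised to intervention versus control". QALYs are to come from EQ-5D over the study period.

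The measurement schedule is in Patient consent, receipt of intervention, and follow-up measurements.

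- **Baseline (t1), both arms.** Patients "complete the baseline (t1) questionnaire, which includes the full TPB measure, the EQ5D, and measures of ethnicity, employment status and education level". Height, weight and demographic details are also recorded. No pedometer reading is part of t1.
- **Control arm.** The information is delivered at the initial session, the t2 questionnaire is completed at the end of it, and the pedometer is handed out then. The text labels the week that follows as the first post-intervention assessment.
- **Intervention arm.** A pedometer is worn for a week before session one. The text limits this to one arm: "This initial assessment of walking constitutes a pre-intervention measurement for those patients in the intervention arm". On t2 it says: "At the end of the second face-to-face session, patients complete the post-intervention (t2) questionnaire", and that session falls two weeks after the initial visit.
- **Later follow-up.** t3 is "six weeks after t2 for both groups". The Analysis section places t4 at six months after t2 in both arms.

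Outcome measures describes walking as "assessed at all time points using the New Lifestyles NL-1000 Activity Monitor Pedometer". The schedule does not bear this out for controls at baseline.

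**The concern.** Two separate problems meet in the economic evaluation.

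First, a comparison between baseline and six months in minutes walked needs a baseline walking value in each arm, and controls have none. No later analysis document can recover a reading that was never taken. An analyst who followed the sentence literally would have to improvise. The obvious improvisation, using the control t2 week as baseline, would set change from before treatment in one arm against change from after treatment in the other.

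Second, t2 falls at different times after enrolment in the two arms, and t4 is timed from t2. Quantities that accumulate from t1, namely costs and QALYs, are therefore observed for longer in the intervention arm. Cost-effectiveness belongs to the third stated aim of the trial (end of Background) and is meant to inform policy, so neither point should be left to be settled once data are in hand.

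**Working it through.** The document gives no figure for the economic window, so there is no stated result to reproduce. The check sets the schedule side by side and does the calendar arithmetic.

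**Step 1: walking measurements by arm** (Patient consent, receipt of intervention, and follow-up measurements)

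| | Control | Intervention |
|---|---|---|
| Pedometer at t1 questionnaire | none | none |
| Pedometer week before the arm's own intervention | 0 | 1 |
| Pedometer week after t2 | 1 | 1 |
| Pedometer at t3 and t4 | yes | yes |

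With 10 practitioners per arm and 20 patients each (Sample size), 10 × 20 = 200 planned controls have no baseline walking value. Minutes walked at baseline against six months can be computed in the intervention arm only. The between-arm difference at t4 can be computed in full.

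**Step 2: baseline-to-t4 interval**, taking six months as 26 weeks

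- Control: t2 = t1 + 0 weeks, so t4 = t1 + 0 + 26 = week 26.
- Intervention: sessions one and two are at weeks 1 and 2, so t2 = t1 + 2 weeks and t4 = t1 + 2 + 26 = week 28. As a check, the final session is at week 4 and also two weeks after session two; 4 − 2 = 2.
- Difference: 28 − 26 = 2 weeks. Ratio: 28/26 = 1.077, or 7.7% longer in the intervention arm.

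**Step 3: what two weeks could be worth in QALYs**

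This assumes that QALYs are summed from t1 to each arm's own t4. The utility is also an assumption, since the document gives none.

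Extra QALYs = utility × 2/52

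| Assumed utility | Extra QALYs, intervention arm |
|---|---|
| 0.6 | 0.023 |
| 0.7 | 0.027 |
| 0.8 | 0.031 |
| 0.9 | 0.035 |

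For scale: EQ-5D is taken only at t1 and t4. With equal utility at t1 and linear interpolation over half a year, a true difference d in utility at t4 yields 0.5 × 0.5 × d = 0.25d QALY. Matching 0.027 to 0.031 QALY would need d = 0.027/0.25 to 0.031/0.25, or about 0.11 to 0.12. If the artefact arises, it could outweigh a genuine effect smaller than that.

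**Step 4: costs**

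The 7.7% applies only to resource use that accrues with time, and only if it is counted from t1 to each arm's own t4. One-off intervention costs are not affected. The document states no recall period or collection date for resource use, so the effect on costs cannot be quantified.

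**The case against.** The strongest reply is that the Economic evaluation section never speaks of *change*. A comparison between baseline and six months may simply name the analysis period. The outcome is a level, minutes per day in the past week; the Analysis section compares arms at each time point; and the section itself refers to six-month outcomes by arm. On that reading the ratio already rests on the six-month difference, and the length of the cost window is detail that a condensed article may leave to a fuller document.

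Much of this stands. It shows that a workable reading exists, and it makes the fix easy. It does not remove the problem: the sentence that defines the ratio names baseline together with the walking outcome, and the two sentences need reconciling.

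Three stronger readings are tempting, and the document does not support them.

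- A reader might infer that the whole cost-effectiveness aim fails. It does not. EQ-5D is collected at t1 and t4 in both arms, so the QALY-based outputs need no baseline walking.
- A reader might infer that the effect estimate will be biased because control t2 readings will stand in for baseline. No part of the document proposes that substitution; it is a risk if the sentence is followed literally.
- A reader might infer that the intervention arm will certainly be credited with extra costs and QALYs. That holds only if each arm accrues to its own t4. With a common horizon the artefact is zero.

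**Conclusion.** The concern holds in a limited form. As worded, the walking ratio cannot be computed for the control arm, and the wording conflicts with the six-month-outcome sentence in the same section. This rests on the stated schedule alone and needs no assumption.

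The two-week difference in the t1-to-t4 interval is also fixed by the schedule. Its consequence is conditional: about 0.027 to 0.031 QALY in favour of the intervention arm if QALYs accrue to each arm's own t4 and utility is 0.7 to 0.8, and nothing if one window is used for both arms.

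The primary analysis is unaffected: its listed covariates do not include baseline walking, and walking is measured at the same time after t2 in both arms. The EQ-5D baseline is available in both arms. The point therefore concerns the economic evaluation only, but it should be settled before the data are analysed.

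**What to change.** 1. Reword the Economic evaluation section so that the effect in the walking ratio is the covariate-adjusted between-arm difference in minutes per day at six months, from the mixed model in the Analysis section. Remove the reference to a baseline comparison for walking.
2. State that the pre-intervention pedometer week, which exists in one arm only, is not used in any between-arm comparison. In Outcome measures, correct the statement that walking is assessed at all time points.
3. Cost and value one identical fixed window from t1 in both arms. Control observation ends at about week 26, so a 26-week window needs no extrapolation. Utility in the intervention arm at that point can be interpolated between t1 and t4.

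Control mailings should not be moved two weeks later to equalise the windows. That would put control walking at 6 + 2 = 8 weeks and 26 + 2 = 28 weeks after t2, against 6 and 26 in the intervention arm, and would break the equal timing of the main outcome for the sake of a secondary analysis.

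The cost is a few sentences, with no extra patients or visits. One thing needs checking: resource use must be recorded so that it can be cut at the chosen week, and the article does not say how it is dated.

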### Analysis

Planned intention-to-treat comparisons of the two groups at one week, six weeks and six months post-intervention (i.e. six months after t2 for both groups) will be conducted, with the primary dependent variable being mean daily walking, as assessed by pedometer. Mixed effects linear models will be fitted to compare the groups with a random practice effect to allow for clustering. The models will adjust for baseline characteristics at both practice and individual level. The former will include practice size and deprivation index, and the latter will include age, gender, BMI, ethnicity, employment status, educational level and clinical condition leading to referral.

As indicated above, the primary response will be the mean daily walking distance observed over up to seven days. Where less than five minutes walking is recorded for any particular day, the reading for that day will be treated as missing, and not used in calculating mean daily duration of walking. When individual days' data are missing, so long as data are available for two or more days, the mean will be taken over these non-missing days. If no data, or data from fewer than two days, are available for a particular patient at a particular timepoint, that assessment of walking will be treated as missing. These missing values will be imputed based on the baseline characteristics of the practice and individual [34]. A secondary analyses will be conducted excluding patients with missing data.

Planned exploratory sub-group analyses will be conducted to determine if the intervention has larger or smaller effects for groups defined in terms of age, ethnicity, gender, socio-economic status, or clinical condition, to provide information on any adverse impacts on social inequality.

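### QALYs rest on EQ-5D at baseline and six months only, so a quality-of-life effect that appears early and then holds or fades is undervalued; the six-week postal pack could carry the missing measurement

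*Protocol article*

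**What the plan says.** In the protocol article, under Patient consent, receipt of intervention, and follow-up measurements, the contents of each questionnaire are set out:

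- **t1 (baseline):** patients "complete the baseline (t1) questionnaire, which includes the full TPB measure, the EQ5D" and some demographic items.
- **t2 (post-intervention):** in the control arm, "patients complete the post-intervention (t2) questionnaire, consisting of the brief TPB measure only". The content is not repeated for the intervention arm, but the measurement procedures are said to be the same in both arms from t2 on.
- **t3 (six weeks after t2):** "all patients are sent a questionnaire by post (t3) containing the brief TPB measure, and a pedometer". No EQ-5D is named.
- **t4 (six months after t2):** "all patients are sent a questionnaire containing a full TPB measure, the EQ5D, and a final pedometer".

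Under Economic evaluation, "Quality of life (EQ-5D) over the study period will be used to generate quality-adjusted life-years (QALYs". These feed incremental cost-effectiveness ratios, acceptability curves and expected net benefit. Cost-effectiveness is the third of the three aims listed in the Background.

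**The concern.** With utility known only at the two ends of follow-up, the QALY calculation has to assume a path between them. A straight line assumes that any benefit builds steadily to six months. The article gives some reason to doubt that shape. The Background reports that walking gains in the earlier volunteer study were maintained for at least six weeks. The Sample size section sets a target of 5 minutes/day against the 12.4 minutes/day seen in the first week of that study, and gives longer follow-up as one of three reasons. An early effect that later weakens is therefore plausible for walking. If quality of life follows walking, which is an assumption, a two-point QALY misses much or all of the benefit.

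The trial will see how walking changes, because the pedometer is worn after t2, at t3 and at t4. It will not see how utility changes. What is at stake is the QALY difference behind the cost per QALY and the net benefit.

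**Working it through.** The article states no EQ-5D or QALY figure, so there is none to reproduce. The proportional errors below do not depend on the size of the gain.

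**Inputs**

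- EQ-5D times: t1 and t4 (from the schedule).
- t3 at 6 weeks and t4 at 26 weeks (0.5 year) from baseline. This is approximate. Both are counted from t2, which falls on the t1 visit in the control arm but about two weeks after t1 in the intervention arm.
- g = difference in utility between arms once the effect is reached. Not given in the article; kept as a symbol, with 0.02 as an assumed illustration.
- Straight lines between measured points (assumed; the article states no interpolation rule).

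**Gain reached at six weeks and held to six months**

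- Two points: g × 0.5/2 = 0.25g.
- Three points: g × (6/52)/2 + g × (0.5 − 6/52) = 0.0577g + 0.3846g = 0.4423g.
- Ratio: 0.25/0.4423 = 0.565, so two points are about 43% too low.
- At g = 0.02: 0.0050 against 0.0088 QALY.

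**Gain peaks at six weeks and fades linearly to zero by six months**

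- Two points: 0, since the arms are equal at both measured times.
- Three points: g × (6/52)/2 + g × (20/52)/2 = 0.25g.
- At g = 0.02: 0 against 0.0050 QALY.

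**Between the two: peak g at six weeks, half of it left at six months**

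- Two points: 0.25 × 0.5g = 0.125g.
- Three points: 0.0577g + (20/52) × (g + 0.5g)/2 = 0.0577g + 0.2885g = 0.3462g.
- Ratio: 0.125/0.3462 = 0.361, so two points are about 64% too low.

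**Gain that builds steadily to six months**

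Two and three points agree at 0.25g, so there is no error.

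**Does the approximate timing matter?** On the intervention arm's calendar, t3 is at 8 weeks and t4 at 28.

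- Held gain, two points: g × (28/52)/2 = 0.269g.
- Held gain, three points: g × (8/52)/2 + g × (20/52) = 0.462g. The shortfall is 1 − 0.269/0.462 = 42%.
- Faded gain: still valued at zero on two points.

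The conclusion does not turn on the two-week offset.

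**The case against.** **The schedule is a choice, not a contradiction.** The economic analysis is not the primary comparison, a short t3 pack spares patients, and baseline to six months is a coherent comparison. The article also plans economic modelling, and "Sensitivity analyses will consider key cost drivers and factors that might affect the outcomes measured". This is fair as to weight. But neither supplies the missing observation. They can only vary an assumed path between t1 and t4.

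**A reader might infer that QALYs will not be adjusted for baseline EQ-5D.** The text does not support this. Economic evaluation states no QALY estimator or covariates, and only says "Economic evaluation methods will, as far as possible, adhere to the recommendations of the NICE Reference Case". The covariate list under Analysis, where "the latter will include age, gender, BMI, ethnicity, employment status, educational level and clinical condition leading to referral", belongs to the walking models. A condensed article commonly leaves the QALY regression to a fuller document, and because EQ-5D is collected at t1, adjustment remains possible.

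**A reader might also infer that interpolation error and chance baseline imbalance exceed any plausible QALY gain.** That is too strong.

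- In the cases above, interpolation error is at most equal to the true gain, never larger.
- For imbalance, every EQ-5D input is an assumption. Take SD 0.25, t1–t4 correlation 0.7 and design effect 1 + 19 × 0.010 = 1.19, the last borrowed from the walking sample size.
- The standard error of the baseline difference is then 0.25 × √(2 × 1.19/200) = 0.0273. If unadjusted, one standard error carries 0.25 × 1.7 × 0.0273 = 0.0116 QALY.
- Six-month utility gains of 0.02, 0.05 and 0.10 give two-point QALY gains (0.25 × gain) of 0.005, 0.0125 and 0.025. The chance that carried imbalance exceeds them is 67%, 28% and 3%. For SD 0.20 to 0.30 the ranges are 59–72%, 18–37% and 1–7%.

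Imbalance would swamp a small gain readily and a large one rarely, and only if no adjustment were made.

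**Conclusion.** The point holds for the measurement schedule. EQ-5D is fixed at t1 and t4 only, so the QALYs misvalue an effect that comes early: about 43% too low if the gain is reached by six weeks and held, and nothing at all if it peaks at six weeks and is gone by six months. These proportions rest on straight lines between points and on approximate timing of 6 and 26 weeks, not on any assumed utility gain. They apply only if the effect has such a shape; a steadily building effect is valued correctly. Whether EQ-5D would follow walking is not known from the article.

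This is a modest design weakness in a stated aim, not an error in the primary analysis. It has to be settled in data collection, because a later analysis plan cannot repair it.

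**What to change.** 1. Under Patient consent, receipt of intervention, and follow-up measurements, add the EQ-5D to the t3 postal questionnaire for both arms.
2. Under Economic evaluation, state that QALYs are computed from t1, t3 and t4, with the times used for each.

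The cost is one short questionnaire in a pack that is already posted. It brings slight extra patient burden and possibly a slightly lower t3 response.

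To confirm in the analysis plan, not as a correction of this article: that the QALY difference is estimated with baseline EQ-5D as a covariate and a practice effect. For a two-point QALY with t1–t4 correlation ρ, the ratio of adjusted to unadjusted variance is (1 − ρ²)/(2 + 2ρ) = (1 − ρ)/2. At assumed correlations of 0.5 and 0.7 this is 0.25 and 0.15, so the standard error falls by 50% and 61%. This needs analysis wording only.
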